### 9.3.3 Visit 2a/5a

As stated in 6.1.1 the advanced session(s) (duration: 240 min) will be performed either on the same day (afternoon after 1 hour recovery brake) or in close as possible/ feasible proximity to V2 (V2a)/V5 (V5a) and prior to treatment start. In dependence of the logistical feasibility and testing capacity, the testing will continue in the voluntary study participants with a sympathetic nerve activity test (MSNA), a transthoracic echocardiography (TTE), a sodium magnetic resonance imaging (Na-MRI) scan and finally a standardized cardiopulmonary exercise test (CPET) and 6-minute walk test (6MWT) (see 9.2).

[figure not shown]

**Fig. 13: Visit 2/5 (Baseline/Final visit, time: -2d to -1d/6w ± 5d): A graphical overview.**

The main study session will be performed in the morning by all enrolled study participants. Patient who voluntarily agreed to participate in the advanced session(s) program will additionally perform the advanced study tests either at the same day (afternoon, after 1 hour recovery brake) or in close proximity to V2/5 (V2a/V5a). Abbreviations: KCCQ: Kansas City cardiomyopathy questionnaire, PSQI: Pittsburgh sleep quality index, PWA: pulse wave analysis, PWV: pulse wave velocity, RVA: Retinal vessel analysis, DVA: Dynamic vessel analysis, FIDa: Flicker-light-induced arterial dilatation, FIDv: Flicker-light-induced venous dilatation, SVA: Static vessel analysis, FMD: Flow-mediated dilatation, GTN: Glyceryl trinitrate test, BIA: Bioimpedance analysis, TBW: Total body water, ICW: Intracellular water, ECW: Extracellular water, DAPA: Dapagliflozin-treatment group, PLA: Placebo-treatment group, MSNA: Muscle sympathetic nerve activity, BV: Blood volume, PV: Plasma volume, RBCV: Red blood cell volume, Hbmass: Total haemoglobin mass, TTE: Transthoracic echocardiography, Na-MRI: Sodium magnet resonance imaging, CPET: Cardiopulmonary exercise testing, 6MWT: 6-minute walk test.

### 9.3.4 Visit 3/4 (V3/4, Follow-up visit 1/2)

The first (V3, time point: 2w, duration: 30 minutes) and second follow-up visit (V4, time point: 6w, duration: 30 minutes) after treatment start will include a clinical evaluation as previously described (see 9.3.2), however without administration tropicamide eye drops. The OpCO measurement will be performed to measure the PVS, the primary outcome variable as well as the BIA to measure TBW and its distribution (ICW/ECW). Furthermore, a specific focus will be on the assessment of potential AEs and defined safety measurements will be assessed as described in section 9.2.4.2.

### 9.3.5 Visit 6 (V6, Follow-up visit of prospective observational study)

The follow-up study visit (V6, time point: 12m post IMP treatment end, duration 240 minutes) of the prospective observational study will include a clinical evaluation as previously described (see 9.3.2). The testing will include the blood volume and body water assessment via OpCO and BIA, arterial stiffness (AS) via planar tonometry, endothelial function via FMD and microvascular function via RVA.

Of note, the follow-up visit V6 is part of the prospective observational study DAPA-VOLVO-Follow-U and following the end of the main study (V5) and will be evaluated and analysed independent from the main study (V2-V5).

## 10. SAFETY

### 10.1 Drug studies

The Sponsor's SOPs provide more detail on safety reporting. The IMP Dapagliflozin has Swiss marketing authorisation and it has been shown in clinical trials to be a safe and well-tolerated drug in patients with heart failure (see also 3.7).

During the entire duration of the main study (V2-V5), all clinically relevant adverse findings, potentially IMP-related (see also 10.1.1, Table 4 Causality: 'Possibly') adverse events (AE) and all serious adverse events (SAEs) are collected, fully investigated and documented in source documents and case report forms (CRF). Study duration of the main study encompasses the time from when the participant signs the informed consent until the last protocol-specific procedure of the main study has been completed.

Of note, visit V6 is an optional follow-up visit 12 months after the final visit V5 of the main study (V2-V5) and part of the prospective observational study DAPA-VOLVO-Follow-U and will be independently evaluated and analysed (see also Fig.1, 5.4, 6.1.1, 10.1, 10.1.3).

During the time period between the end of the main study (final visit: V5) and the optional visit V6 without interventions AEs will not be recorded.

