### **4.4 Safety Objectives**

The study aims to assess whether dapagliflozin leads to a differential adverse profile (e.g. incidences of hypotension, renal dysfunction, genital infections (GI) and urinary tract infections (UTI), diabetic ketoacidosis, etc.) and general adverse event profile in comparison to placebo.

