## **9.2.4 Assessment of safety outcomes**

### **9.2.4.1 Adverse events**

Serious adverse events will be routinely assessed and recorded on main study visits (V2 to V5). The definition and way of such events to be assessed and reported is defined in section 10. On each visit V2-V5, standardized questions on the occurrence of any adverse events will be conducted.

Spontaneous events will also be recorded in the eCRF and reported as defined in section 10.

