### **9.2.4.2 Laboratory parameters**

Prespecified safety laboratory parameters are eGFR and NT-proBNP.

They will be assessed on each visit (V1-5) of the main study and sampled as described in section 9.2.3.

The following parameter is to be documented as an adverse event:

eGFR < 20 mL/min/1.73m^2 (CKD-EPI formula) or eGFR decrease > 50% of baseline;

Any aberration in other laboratory parameters that are assessed as described in section 9.2.3 and are regarded clinical significant by the investigator are to be documented as an adverse event.

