#### 10.1.1 Definition and assessment of (serious) adverse events and other safety related events

An **Adverse Event (AE)** is any untoward medical occurrence in a patient or a clinical investigation participant administered a pharmaceutical product and which does not necessarily have a causal relationship with the study procedure. An AE can therefore be any unfavourable and unintended sign (including an abnormal laboratory finding), symptom, or disease temporally associated with the use of a medicinal (investigational) product, whether or not related to the medicinal (investigational) product. [ICH E6 1.2]

A **Serious Adverse Event (SAE)** is classified as any untoward medical occurrence that:

- results in death,
- is life-threatening,
- requires in-patient hospitalization or prolongation of existing hospitalisation,
- results in persistent or significant disability/incapacity, or
- is a congenital anomaly/birth defect.

In addition, important medical events that may not be immediately life-threatening or result in death, or require hospitalisation, but may jeopardise the patient or may require intervention to prevent one of the other outcomes listed above should also usually be considered serious. [ICH E2A]

Examples of such events are intensive treatment in an emergency room or at home for allergic bronchospasm, blood dyscrasias or convulsions that do not result in hospitalisation, or development of drug dependency or drug abuse.

SAEs should be followed until resolution or stabilisation. Participants with ongoing SAEs at study termination (including safety visit) will be further followed up until recovery or until stabilisation of the disease after termination.

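### Section 10.1 restricts which non-serious adverse events reach the CRF by judged relatedness or clinical relevance, in conflict with 4.4, 5.4, 9.2.4.1 and 10.1.1, leaving the general comparison with placebo incomplete

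*Protocol*

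**What the plan says.** The collection rule is in Protocol 10.1. It begins "During the entire duration of the main study (V2-V5), all clinically relevant adverse findings" and continues with "potentially IMP-related (see also 10.1.1, Table 4 Causality: 'Possibly') adverse events (AE) and all serious adverse events (SAEs) are collected", all to be documented in source documents and the CRF. Three routes are therefore open: clinical relevance, possible relatedness and seriousness.

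Other sections are wider:

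- **4.4 Safety Objectives** covers specific event types and also the "general adverse event profile in comparison to placebo".
- **5.4 Safety Outcomes** lists AEs and SAEs together with no causality condition. It lists hypotension, genital and urinary tract infections, ketoacidosis, Fournier gangrene and back pain as separate outcomes.
- **9.2.4.1 Adverse events** says that at V2 to V5 "standardized questions on the occurrence of any adverse events will be conducted". It adds: "Spontaneous events will also be recorded in the eCRF and reported as defined in section 10". Its sentence on routine assessment and recording names serious events only.
- **9.2.4.2 Laboratory parameters** makes defined eGFR falls adverse events, and says that other laboratory aberrations that "are regarded clinical significant by the investigator are to be documented as an adverse event".
- **10.1.1** defines an adverse event as any untoward occurrence, "whether or not related to the medicinal (investigational) product".

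Section 11.4.5 makes the safety analysis descriptive, without formal inference.

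**The concern.** In a randomised placebo-controlled trial, the difference between arms is the main evidence on whether an event is caused by the drug. If an opinion on causality in the individual patient decides whether an event is recorded, that opinion comes before the comparison meant to inform it. An unexpected effect, which nobody yet attributes to the drug, is the kind most likely to be filtered out.

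The loss would be permanent. A statistical analysis plan can choose how to tabulate recorded events, but it cannot recover events that never entered the database. Section 11.4.4 also makes the descriptive evaluation of the safety outcomes the trigger for a possible unplanned interim analysis, so incomplete AE data would weaken that trigger.

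There is a practical problem as well. Staff ask each patient about any adverse event at every main-study visit, and then find no consistent instruction on which answers to enter.

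**Working it through.** No arithmetic applies, because the document gives no AE rate and no rate of attribution. The check is to follow a non-serious adverse event through the sections and see where it is captured.

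**Step 1: elicitation.** Under 9.2.4.1 the patient is asked about any adverse event at V2 to V5. Relatedness plays no part at this stage.

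**Step 2: definition.** Under 10.1.1 the event is an AE whatever its cause.

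**Step 3: entry under 10.1.** The event enters the CRF if it is a clinically relevant finding, or if it reaches the level Possibly in Table 4 (read here as that level or higher). Table 4 asks for a temporal relationship with another cause possible. Unlikely covers assessable reactions that do not meet the levels above it, and Not related requires that causality can be ruled out. The bar for Possibly is low but leaves room for judgement. Clinical relevance is not defined in 10.1.

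**Step 4: other routes.** Laboratory events are captured through 9.2.4.2 whatever their cause. The named events in 5.4 are outcomes in their own right and carry no causality condition.

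**Step 5: does 9.2.4.1 close the gap?** Not clearly. It sends spontaneous events to the eCRF, which is wider than 10.1. But it refers to section 10 for reporting, and section 10 holds the restriction. Its routine-recording sentence is limited to serious events, and no sentence says that every event elicited by the standardised questions is entered. Section 10.1.3 again pairs ongoing SAEs with potentially IMP-related AEs when it defines who returns for follow-up, so the restriction in 10.1 does not look like a slip of wording.

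**Step 6: what is left out.** An event lacks a clear route into the CRF only if all of these hold:

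1. it is not serious;
2. it is rated Unlikely or Not related;
3. it is not considered clinically relevant, in the laboratory or otherwise;
4. it is not one of the named safety outcomes.

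**Step 7: size.** Conditions 2 and 3 rest on investigator judgement, and the document gives no frequency for either. The loss could lie anywhere from none to all of the non-serious events outside the named outcomes. It cannot be narrowed from the document.

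**The case against.** The best defence is that the protocol already captures what matters most. All serious events, all clinically relevant findings, significant laboratory changes and the drug-related events named in 5.4 are collected without a causality test. Possibly is an easy level to reach under daily dosing, so few events may be lost. Section 6.2.2 keeps investigators and assessors blind until database lock, so the filter should act alike in both arms. The analysis is descriptive, and 11.4.5 refers to 9.2.4 for its outcomes, not to 10.1. The product has Swiss marketing authorisation, and 10.1 refers to sponsor SOPs, not available here, for more detail on safety reporting. A sponsor may choose selective recording of non-serious events, and the conflict could equally be removed by narrowing 4.4 and 5.4.

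Much of this stands, and it limits the point. A reader might infer that the objective in 4.4 cannot be met at all. The document does not support that, because a comparison by arm remains possible on a large part of the safety data. A reader might also infer that the AE table would show differences in attribution instead of differences in incidence. That would need attribution to differ between arms, for example through staff recognising typical effects of the drug class. The protocol gives no evidence of this, and several such effects are separate outcomes anyway. Nor can a number of lost events be put forward: it would rest on an assumed attribution rate and would have to allow for the clinical-relevance route.

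The defence does not remove the contradiction. A filter that acts equally in both arms still loses events and thins a table with 40 patients per arm. Unseen SOPs do not tell the reader of the protocol which section governs.

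**Conclusion.** The concern holds as an internal conflict with a limited consequence. Section 10.1 is narrower than 4.4, 5.4, 9.2.4.1 and 10.1.1, and the protocol does not say which prevails. If 10.1 is followed as written, the general AE comparison with placebo is incomplete, and dependent on investigator judgement, for the events that meet all four conditions set out above.

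The size of the loss is unknown. Bias between arms is possible but not shown. The conclusion assumes that 10.1 is the operative rule for CRF entry and that the SOPs do not override it. The change should be made, because the gap cannot be repaired at the analysis stage and the remedy is cheap.

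**What to change.** Amend 10.1 so that every adverse event reported from V2 to V5 is entered in the eCRF, with the Table 4 causality rating as a graded field and no longer as a condition of entry. Align 9.2.4.1 by stating that all events elicited by the standardised questions, as well as spontaneous ones, are recorded, serious or not. Tabulate all AEs by arm first, and those rated Possibly or higher as a second table.

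The cost is some extra data entry for 80 patients over 12 weeks. The visits and the questions are already planned. Narrowing 4.4 and 5.4 would also remove the contradiction, but it would give up the general AE comparison that the protocol sets out to make.

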#### 10.1.1 Definition and assessment of (serious) adverse events and other safety related events

An **Adverse Event (AE)** is any untoward medical occurrence in a patient or a clinical investigation participant administered a pharmaceutical product and which does not necessarily have a causal relationship with the study procedure. An AE can therefore be any unfavourable and unintended sign (including an abnormal laboratory finding), symptom, or disease temporally associated with the use of a medicinal (investigational) product, whether or not related to the medicinal (investigational) product. [ICH E6 1.2]

A **Serious Adverse Event (SAE)** is classified as any untoward medical occurrence that:

- results in death,
- is life-threatening,
- requires in-patient hospitalization or prolongation of existing hospitalisation,
- results in persistent or significant disability/incapacity, or
- is a congenital anomaly/birth defect.

In addition, important medical events that may not be immediately life-threatening or result in death, or require hospitalisation, but may jeopardise the patient or may require intervention to prevent one of the other outcomes listed above should also usually be considered serious. [ICH E2A]

Examples of such events are intensive treatment in an emergency room or at home for allergic bronchospasm, blood dyscrasias or convulsions that do not result in hospitalisation, or development of drug dependency or drug abuse.

SAEs should be followed until resolution or stabilisation. Participants with ongoing SAEs at study termination (including safety visit) will be further followed up until recovery or until stabilisation of the disease after termination.

#### Assessment of Causality

Both Investigator and Sponsor-investigator make a causality assessment of the event to the study drug, based on the criteria listed in the ICH E2A guidelines:

**Table 4:** Categories of causality assessment.

| Relationship        | Description           |
|---------------------|-----------------------|
| Causal relationship | Temporal relationship |

|                                                                                         |                                                                                                  |
|-----------------------------------------------------------------------------------------|--------------------------------------------------------------------------------------------------|
|                                                                                         | Improvement after dechallenge*
Recurrence after rechallenge
(or other proof of drug cause) |
| Probably                                                                                | Temporal relationship
Improvement after dechallenge
No other cause evident                 |
| Possibly                                                                                | Temporal relationship
Other cause possible                                                    |
| Unlikely                                                                                | Any assessable reaction that does not fulfil the above conditions                                |
| Not related                                                                             | Causal relationship can be ruled out                                                             |
| *Improvement after dechallenge only taken into consideration, if applicable to reaction |                                                                                                  |

### Unexpected Adverse Drug Reaction

An “unexpected” adverse drug reaction is an adverse reaction, the nature or severity of which is not consistent with the applicable product information. [ICH E2A]

### Suspected Unexpected Serious Adverse Reactions (SUSARs)

The Sponsor-Investigator evaluates any SAE that has been reported regarding seriousness, causality and expectedness. If the event is related to the investigational product and is both serious and unexpected, it is classified as a SUSAR.

Unblinding is needed in order to determine a SUSAR. Treatment allocation should not be disclosed to the investigator, nor to the study staff, in order not to make the subject ineligible.

### Assessment of Severity

For severity grading of AEs in this study, depending on the type of study and disease, the grades for severity are described in the “Common Terminology Criteria for Adverse Events (CTCAE) version 5.0 terminology [118].

#### 10.1.2 Reporting of serious adverse events (SAE) and other safety related events

The investigators are responsible for SAE reporting to the CEC according to the following details:

#### Reporting of SAEs

All SAEs must be reported immediately and within a maximum of 24 hours to the Sponsor-Investigator of the study. The Sponsor-Investigator will re-evaluate the SAE and return the form to the site.

SAEs resulting in death are reported to the Ethics Committee via BASEC within 7 days.

There are no SAEs that are exempted from expedited reporting.

SAEs or other safety relevant events must be also reported to the Marketing Approval Holder (MAH) of the drug (AstraZeneca AG). The details are documented in the Global PS guideline for externally sponsored research (ESR) document (Version 4, 8th February 2019, see APPENDICES) provided by AZ.

#### Reporting of SUSARs

A SUSAR needs to be reported to the Ethics Committee (local event via local Investigator) via BASEC and to Swissmedic (via Sponsor-Investigator) within 7 days, if the event is fatal, or within 15 days (all other events).

#### Reporting of Safety Signals

All suspected new risks and relevant new aspects of known adverse reactions that require safety-related measures, i.e. so called safety signals, must be reported to the Sponsor-Investigator within 24 hours. The Sponsor-Investigator must report the safety signals within 7 days to the Ethics Committee (local event via local Investigator) via BASEC and to Swissmedic.

### **Reporting and Handling of Pregnancies**

During the screening visit prior to the study enrolment (see also 9.3.1) a pregnancy test will be performed in premenopausal (or postmenopausal < 2 years) female patients with child bearing potential. Furthermore, these patients will be instructed orally and in written form (study information sheet, PIC) to use reliable forms of contraception throughout the study period and for additional 3 months thereafter.

Pregnancy itself is not regarded as an AE unless there is a suspicion that the investigational product under study may have interfered with the effectiveness of a contraceptive medication.

Pregnant participants must immediately be withdrawn from the clinical study. Any pregnancy during the treatment phase of the study and within 30 days after discontinuation of study medication will be reported to the Sponsor-Investigator within 24 hours. The course and outcome of the pregnancy will be followed up carefully, and any abnormal outcome regarding the mother or the child must be documented and reported.

### **Periodic reporting of safety**

An annual safety report is submitted once a year to the local Ethics Committee via local Investigator and to Swissmedic via Sponsor-Investigator.

#### **10.1.3 Follow up of Serious Adverse Events**

Participants terminating the main study (V2-V5) (either regularly or prematurely) with reported ongoing SAE

any ongoing potentially IMP-related AEs will return for a follow-up investigation.

This visit will take place up to 30 days after terminating the treatment period.

Follow-up information on the outcome will be recorded on the respective AE page in the eCRF.

All other information has to be documented in the source documents. Source data has to be available upon request.

In case of participants lost to follow-up, efforts should be made and documented to contact the participant to encourage him/her to continue study participation as scheduled.

Follow-up investigations may also be necessary according to the investigator's medical judgment even if the participant has no SAE at the end of the study.

## 11.2 Determination of Sample Size

A sample size estimation was performed for the primary study outcome ( $\Delta$ PVS) using R (V3.6.1) and PASS (V20.0.1). The sample size calculation comprised 2 primary analyses, which lead to the conclusion that a total sample size of 80 patients is sufficient to reach a power of  $\geq 80\%$  for the primary outcome test analysis (mixed model for repeated measures, MMRM):

